## Abstract

**Background:**

Law enforcement officers are routinely exposed to hazardous, disturbing events that can impose severe stress and long-term psychological trauma. As a result, police and other public safety personnel (PSP) are at increased risk of developing posttraumatic stress injuries (PTSIs) and disruptions to the autonomic nervous system (ANS). ANS functioning can be objectively and noninvasively measured by heart rate (HR), heart rate variability (HRV), and respiratory sinus arrhythmia (RSA). Traditional interventions aimed at building resilience among PSP have not adequately addressed the physiological ANS dysregulations that lead to mental and physical health conditions, as well as burnout and fatigue following potential psychological trauma.

**Objective:**

In this study, we will investigate the efficacy of a web-based Autonomic Modulation Training (AMT) intervention on the following outcomes: (1) reducing self-reported symptoms of PTSI, (2) strengthening ANS physiological resilience and wellness capacity, and (3) exploring how sex and gender are related to baseline differences in psychological and biological PTSI symptoms and response to the AMT intervention.

**Methods:**

The study is comprised of 2 phases. Phase 1 involves the development of the web-based AMT intervention, which includes 1 session of baseline survey measures, 6 weekly sessions that integrate HRV biofeedback (HRVBF) training with meta-cognitive skill practice, and 1 session of follow-up survey measures. Phase 2 will use a cluster randomized control design to test the effectiveness of AMT on the following prepost outcomes: (1) self-report symptoms of PTSI and other wellness measures; (2) physiological indicators of health and resilience including resting HR, HRV, and RSA; and (3) the influence of sex and gender on other outcomes. Participants will be recruited for an 8-week study across Canada in rolling cohorts.

**Results:**

The study received grant funding in March 2020 and ethics approval in February 2021. Due to delays related to COVID-19, phase 1 was completed in December 2022, and phase 2 pilot testing began in February 2023. Cohorts of 10 participants in the experimental (AMT) and control (prepost assessment only) groups will continue until a total of 250 participants are tested. Data collection from all phases is expected to conclude in December 2025 but may be extended until the intended sample size is reached. Quantitative analyses of psychological and physiological data will be conducted in conjunction with expert coinvestigators.

**Conclusions:**

There is an urgent need to provide police and PSP with effective training that improves physical and psychological functioning. Given that help-seeking for PTSI is reduced among these occupational groups, AMT is a promising intervention that can be completed in the privacy of one’s home. Importantly, AMT is a novel program that uniquely addresses the underlying physiological mechanisms that support resilience and wellness promotion and is tailored to the occupational demands of PSP.

**Trial Registration:**

ClinicalTrials.gov NCT05521360; https://clinicaltrials.gov/ct2/show/NCT05521360

**International Registered Report Identifier (IRRID):**

PRR1-10.2196/33492

## Introduction

### Background

Law enforcement officers are routinely exposed to hazardous, disturbing events that can impose severe stress and long-term psychological trauma. Upward of 42% of public safety personnel (PSP) report one or more mental health symptoms [1]. Accumulated stress and posttraumatic stress injuries (PTSIs) result in chronic physical and mental health disorders, including anxiety, depression, substance abuse, and cardiovascular disease [2,3]. PTSI is also related to reduced occupational performance, absenteeism, and risky behavior, with implications for both police and public safety [4,5]. Recent empirical research and government reports have highlighted a mental health and suicide crisis among various PSP sectors in Canada [6-8]. The accumulated evidence forms an urgent call for evidence-based programs that build resilience and wellness capacity in order to prevent PTSI symptoms before they manifest as severe, chronic, diagnosable disorders in PSP.

### Biological Resilience: The Missing Piece

Existing PTSI prevention and resilience promotion interventions tailored to PSP not only show limited effectiveness but also do not consider sex and gender as central determinants of health and variables of importance [5,9,10]. Further, most traditional interventions are focused on addressing cognitive, emotional, and behavioral components without addressing the underlying neurophysiological mechanisms that erode resilience [2,11-14]. Typically, when a person encounters stress (either real or imagined), they will experience characteristic changes in the autonomic nervous system (ANS), including increased sympathetic nervous system (SNS) activation that elevates heart rate (HR) and respiration and a withdrawal of parasympathetic nervous system (PNS) activation. When stress has abated, PNS activation will lower heart and breathing rates and blood pressure, helping the body to return to reparative and restorative functioning [15].

Advances in physiology and neuroscience demonstrate that resilience is maintained by healthy ANS functioning. Disruptions in ANS functioning can be observed by objectively and noninvasively measuring 2 biological indices [13,14,16]: heart rate variability (HRV) and respiratory sinus arrhythmia (RSA). HRV is the variation in the time between successive heartbeats and depends primarily on the extrinsic regulation of HR by the balance between the SNS and PNS branches of the ANS [17,18]. If the time between heartbeats is rather constant, HRV will be low, whereas if the time varies, HRV will be higher. When a person is at rest, a high HRV signals good health because it represents a physical indicator of autonomic flexibility in responding to challenges [18,19]. In contrast, low resting HRV signals an imbalance in autonomic function, such as in clinical cases of anxiety and psychopathology, where there is an overactivation of the sympathetic branch and a weakening of parasympathetic influence over the heart [20]. RSA refers to the synchronization of HRV with breathing such that HR speeds up during inhalation (shortening the time between heartbeats) and slows during exhalation (lengthening the time between heartbeats) [21,22]. Increasing RSA builds physical wellness capacity by strengthening an individual’s long-term reserves, which is theorized to occur via multiple pathways (ie, baroreflex control, blood pressure regulation, and efficiency of pulmonary gas exchange) [21,23].

There is evidence to suggest sex can influence ANS functioning, as indicated by differences in HRV and RSA at rest [24]. These findings have direct implications for evaluating and understanding biological resilience and the effectiveness of psychophysiological interventions. Policing is known to be both intensely stressful [25] and a hypermasculinized profession [26,27], both of which have significant consequences for women’s professional experiences of stress and health. What remains to be seen is whether sociocultural gender and related occupational stressors (eg, gender discrimination and harassment) might contribute to differences in biological functioning and the effectiveness of physiologically focused wellness interventions.

### Biological Resilience Training: Heart Rate Variability Biofeedback

Research reveals a connection between respiration, arousal, and emotional control, such that how a person breathes sends signals to regions in the brainstem and forebrain that modulate arousal [28]. For example, periods of slow breathing are associated with SNS suppression and PNS stimulation, which may underlie the anxiety- and stress-reducing effects of RSA [28]. For nearly 3 decades, Lehrer and Gevirtz [21] have pioneered and refined a cardiorespiratory intervention called heart rate variability biofeedback (HRVBF). During HRVBF, a person is shown visual feedback of their beat-by-beat HR data while engaging in slow breathing with the goal of maximizing RSA. For clinically effective treatment, it is not sufficient to simply instruct a person to breathe slowly. Rather, HRVBF technology is required to identify the precise breathing rate for maximizing individual RSA and to condition this rate through training [29,30].

In collaboration with expert police practitioners as well as medical and academic experts in psychophysiological risk and resilience, the lead author developed the International Performance Resilience and Efficiency Program (iPREP), an in-person resilience program that improves occupational health and performance by addressing the unique acute and chronic stressors faced by police [31-33]. This program has been refined across 6 grant-funded multimethod studies with over 300 police participants measuring objective psychophysiological and behavioral data [31-40]. The components of the currently proposed intervention are based upon the same core scientific principles and validated intervention methods as iPREP, including mental health awareness and support [2] and psychophysiological techniques (ie, HRVBF) to promote resilience by conditioning adaptive HRV, RSA, and HR functioning [30,41,42]. Research has shown that the autonomic modulation techniques instructed during iPREP result in significant, long-term reductions in occupational errors and improvements in officers’ ability to recover quickly from acutely stressful events when completed during scenario-based, in-person training [31-33].

### Objectives

The aim of the proposed study is to develop (phase 1) and test (phase 2) if a web-based delivery of autonomic modulation training (AMT) can reduce symptoms of PTSI and build psychological wellness capacity and physiological resilience in police officers with similar effectiveness as in-person training. An additional novel scientific contribution of this protocol includes an examination of sex and gender in baseline biological and psychological presentations of PTSI among police and in response to a resilience-building intervention.

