### Recruitment

We aim to test the AMT intervention on a sample of approximately 250 frontline police officers in rolling cohorts of 10-15 participants (half AMT, half waitlist control) from geographically representative police services across Canada. A power analysis was conducted using G*Power software [43] and found that a minimum total sample size of 128 participants was required (effect size f=0.25, α=.05, power=0.80, number of groups=2, number of repeated measures=2). However, we plan to oversample officers by sex and mitigate possible attrition based on the principal investigator’s previous experience with conducting longitudinal research on police officers [31-33]. A small laboratory-based prepilot sample (n=10) will test equipment reliability, accuracy, and integration of HR monitors with HRVBF and learning management system (LMS) platforms. An initial pilot cohort 1 (n=30) will then test the AMT intervention in the population of interest (ie, law enforcement officers) using a combined laboratory-remote paradigm to validate the implementation of study procedures. These participants will also be invited to participate in a poststudy focus group as per the study protocol (see iKT Focus Groups in Procedures) to optimize the intervention (ie, content and delivery) and overall study procedures to provide stakeholder- and user-informed feedback. When all user feedback has been incorporated, all subsequent participants will be tested fully remotely and in accordance with the randomized control trial procedures and group allocation.

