##### Session 1: Preintervention Assessment (1.5 Hours)

During this session participants will complete self-reported baseline measures of: (1) PTSI, including the Personal Health Questionnaire (PHQ-8) for major depressive disorder, General Anxiety Disorder Scale (GAD-7), Depression, Anxiety, and Stress Scale (DASS-42), PTSD checklist (PCL-5), Alcohol Use Disorder Identification Test (AUDIT), Perceived Stress Scale (PSS), and Personal Burnout Subscale of the Copenhagen Burnout Inventory (CBI) [65-71]; (2) resilience and well-being using the Brief Coping Orientation to Problems Experienced Inventory (Brief-COPE), Resilience Scale for Adults (RSA-33), Brief Resilience Scale (BRS), White Bear Suppression Inventory (WBSI), Perseverative Thinking Questionnaire (PTQ), Ultra Brief-Penn State Worry Questionnaire (UB-PSWQ), and Ultra Brief-Rumination Response Styles (UB-RRS) Questionnaire [72-78]; (3) functional wellness and occupational stress using the Sheehan Disability Scale (SDS), Good Health Practices Scale (GHPS), COVID-19 adapted version of the Holmes Rahe Stress Inventory (COVID-19 HRSI), World Health Organization Disability Assessment Scale (WHODAS 2.0) [79-82], operational and organizational subscales of the Police Stress Questionnaire (PSQ) [83], and Lam Employment Absence and Productivity Scale (LEAPS) [84]; and (4) sex and gender-relevant data using the Workplace Gender Discrimination Scale (WGDS) and Gender Experiences Questionnaire (GEQ) [85,86]. Global ratings of stress will be asked at the beginning of each AMT session using a sliding visual analog scale of 0 (not at all stressful) to 10 (extremely stressful) in response to 2 questions: “How stressful was this past week?” and “How stressed are you right now?.” Data will be immediately tabulated to randomly assign participants matched on demographic and outcome variables to either the experimental AMT intervention group that will continue with sessions 2-8 of the protocol or to the waitlist control group that will only be responsible for the first part of session 2 and all of session 8 (postintervention assessment).

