##### Session 2: Baseline Physiological Assessment and Introduction to AMT (40-60 Minutes)

All participants will be taught via web-based video modules how to apply the wearable HR monitor and configure the HRVBF app. The wearable HR monitor will automatically record date and time-stamped physiological data upon contact with the skin via the chest band and will communicate with the HRVBF app via Bluetooth. All HRV data will be stored locally on the HRVBF app and study device, which will be mailed back to the research team at the end of the study period. In the first part of this session, both experimental and control participants will provide baseline resting HRV and RSA data that will be recorded while participants engage in a 7-minute neutral activity (eg, listening to prerecorded sounds) that does not stimulate arousal or relaxation ([name], unpublished data, 2019). To assess recovery from an acute stressor, participants will perform web-based versions of the Paced Auditory Serial Addition Test (PASAT) [87] and the emotional Stroop task [88], both of which have been shown to induce significant sympathetic arousal but do not simulate traumatic material [28].

Following these baseline physiological assessments, participants in the experimental group will continue with the rest of their session (15-20 min) and begin the AMT intervention. Participants in the control group will not have any programming until session 8 (postintervention assessment).

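### The Objectives set out to show effectiveness similar to in-person training, but the randomized comparison with a waitlist cannot establish that

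*Protocol article*

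**What the plan says.** The aim in the Objectives section of the protocol article has two parts: to develop web-based AMT, and to test whether it can reduce PTSI symptoms and "build psychological wellness capacity and physiological resilience in police officers with similar effectiveness as in-person training". The comparison with in-person delivery belongs to what is to be tested. It is not offered as background.

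The comparator is described in several places, and the descriptions agree:

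- Recruitment plans "rolling cohorts of 10-15 participants (half AMT, half waitlist control".
- The Abstract (Results) has "Cohorts of 10 participants in the experimental (AMT) and control (prepost assessment only) groups will continue until a total of 250 participants are tested".
- The Session 1 section assigns the others to "the waitlist control group that will only be responsible for the first part of session 2" and to session 8.
- The Session 2 section adds: "Participants in the control group will not have any programming until session 8 (postintervention assessment".

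Delivery after the pilot is also fixed in Recruitment: "all subsequent participants will be tested fully remotely and in accordance with the randomized control trial procedures and group allocation".

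In-person training appears as background. The section on heart rate variability biofeedback describes the team's in-person programme (iPREP) and says that its techniques "result in significant, long-term reductions in occupational errors" and help officers recover from acute stress.

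**The concern.** A trial can support a claim about two ways of delivering a programme only if it observes both, or if it sets out how it will bring in outside evidence on the one it does not observe. Here one side of the stated comparison is absent.

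What is at stake is the claim. If the phrase stays in the declared aim, a significant result against waitlist could be reported or read as having met the whole aim. A police service choosing between web and in-person delivery would then be relying on something the trial did not examine. The Discussion looks ahead to wider implementation if AMT is found effective, so the wording of the aim has practical weight.

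**Working it through.** **1. Each design element against the stated aim**

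| Element (section of the protocol article) | What it contains | Bears on web versus in-person? |
|---|---|---|
| Randomized arms (Recruitment; Session 1) | AMT versus waitlist | No |
| Control arm between assessments (Session 2) | No programming | No |
| Controls after session 8 (Session 8) | Offered the web-based sessions 3 to 7 | No, still web-based |
| Delivery after the pilot (Recruitment) | Fully remote | No |
| Pilot cohort, n = 30 (Recruitment) | Run "using a combined laboratory-remote paradigm to validate the implementation of study procedures" | No, a check of procedures and not an in-person comparator |
| H1, H2, H4 to H6 (Hypotheses) | Improvement after AMT | No |
| H3, H7 (Hypotheses) | Sex and gender differences | No |
| Analyses (Data Security and Analyses) | Pre-post repeated measures ANCOVAs, regressions on predictors, weekly change within AMT | No |
| Power analysis (Recruitment) | Two-group calculation, f = 0.25 | No margin given |

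**2. What the power analysis was sized for**

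Inputs from Recruitment: f = 0.25, α = 0.05, power 0.80, two groups, two repeated measures, minimum total 128.

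- For two equal groups, d = 2f = 2 × 0.25 = 0.5.
- Normal approximation: n per arm = 2(1.96 + 0.8416)² / 0.5² = 2 × 7.849 / 0.25 = 62.8, so 63 per arm and 126 in total.
- Exact noncentral F, single measurement: 128 in total. The plan's figure is reproduced.

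With two repeated measures, the between-group total would be 98 at a correlation of 0.5 and would reach 128 only at a correlation of 1. The stated figure is therefore that of a single-measurement comparison. This does not affect the present point, because every variant is a test for a difference.

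At the planned 250 (125 per arm), power for d = 0.5 is Φ(0.5 × √(125/2) − 1.96) = Φ(3.953 − 1.96) = Φ(1.993) ≈ 0.98, ignoring clustering, attrition and multiplicity. On those terms the trial is well sized for AMT versus waitlist.

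**3. Why that gives no answer on similarity**

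Let W, C and I be the mean outcomes under web-based AMT, waitlist and in-person training. The trial estimates W − C. The aim concerns W − I, and

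W − I = (W − C) − (I − C).

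The second bracket, the effect of in-person training over no training on these outcomes, is neither observed in the trial nor given in the article. Suppose W − C came out at the design value of 0.5 SD. Then W − I = 0.5 − (I − C), which is zero only if the in-person effect also happens to be 0.5 SD. More participants make the first bracket more precise and leave the second unknown. The contrast is therefore not estimable from this trial at any sample size.

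**4. Consistency within the article**

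The Abstract objective speaks of the efficacy of the web-based intervention. The HRVBF Training section notes that the source protocol was meant for in-person use and says this project tests how well web delivery works in police. Both fit the waitlist design. The closing phrase of the aim in the Objectives does not.

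**The case against.** **The phrase is one clause, and the rest of the article fits the design.** This is largely right. The hypotheses, the analyses and the Discussion all concern whether AMT works, and the Discussion nowhere says that web delivery is as good as in-person. That limits the point to the wording of the aim. It does not remove it, because the Objectives section is where the claim to be tested is declared.

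**An article condenses a fuller protocol, and an analysis plan may exist.** A benchmark against earlier data could be described in a document not shown here, so the most that can be said is that the article describes none. But the comparator is fixed by the randomization, and no analysis plan can add an in-person arm.

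Four stronger readings are tempting, and the documents do not support them:

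- *That no indirect comparison with in-person training is possible.* The article says in-person iPREP helped officers recover from acute stress, and H6 concerns recovery from acute stress, although with web-based PASAT and Stroop tasks. It says the earlier studies took psychophysiological measurements in over 300 police, and it cites meta-analyses reporting a large effect of HRVBF on self-reported anxiety and stress. What those sources contain cannot be judged from here. A non-randomized benchmark is conceivable; none is described.
- *That the controls have no contact.* They complete session 1, receive equipment, do the first part of session 2, get an email reminder and complete session 8. What they lack is programming.
- *That the trial says nothing about similarity whatever its result.* No result can establish similarity, but a clear failure against waitlist would count informally against it.
- *That the trial is too small for a non-inferiority comparison.* The documents give no margin and the trial has no in-person arm, so any such sample size would rest on an invented margin for an arm that does not exist.

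**Conclusion.** The concern holds as a mismatch between the stated aim and the design. The Objectives declare a test of similarity to in-person training. The trial randomizes against a waitlist without programming, and the article describes no in-person arm, margin, delivery-mode hypothesis or planned benchmark. A positive result would show that web-based AMT beats no training, which is a useful finding, but it would not show that AMT matches in-person delivery.

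The size of the problem is one phrase in the aim. It biases no estimate, and the AMT-versus-waitlist comparison is not invalidated by it. It should still be corrected, because the aim determines what a positive result may be said to show.

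The conclusion rests on the article's own account of arms, hypotheses and analyses. It needs no assumed effect size or margin.

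**What to change.** In the Objectives, delete the phrase about similarity to in-person training and state the aim in line with the Abstract objective. For example:

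> Phase 2 will test the effectiveness of web-based AMT, compared with a waitlist control, on the self-reported and physiological outcomes at session 8. The randomized comparison does not support a conclusion about web versus in-person delivery. Any comparison with earlier in-person data would be non-randomized and will be labelled exploratory.

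The last sentence leaves the team free to set its results beside its earlier in-person work, provided the status of that comparison is clear.

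The cost is a few sentences in one section and a narrower claim. No change to sample size, conduct or analysis is needed.
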